### Follow-up

We will implement the following plans to promote participant retention and complete follow-up:
•Regular follow-up appointments and communication to encourage participants to complete the study.•Collecting contact information and maintaining updated records for all participants.•Clearly outlining the importance of continued participation and the potential consequences of non-completion at the informed consent stage.

## Methods: monitoring

A Data Monitoring Committee is not deemed necessary for this study due to its relatively low-risk nature and the absence of interim analyses or stopping guidelines. Interim analyses are not planned for this study, and as such, there are no specific stopping guidelines. The final decision to terminate the trial will be made by the principal investigator in consultation with the research team.

### Adverse events and unintended effects

We will implement systematic procedures for collecting, assessing, reporting, and managing adverse events. Adverse events will be documented by the clinical research team, assessed for causality and severity, and reported to the appropriate regulatory authorities as per regulatory requirements.

### Auditing trial conduct

An independent auditing process for trial conduct will not be conducted, as the study is not expected to pose significant risks to participants. However, regular internal quality control checks and monitoring of data integrity will be performed throughout the study to ensure data accuracy and adherence to the protocol.

### Primary outcome measures

**Effectiveness assessment:**
1.
**Regression of cysts:** To monitor the regression of ovarian cysts, we will conduct regular ultrasound evaluations. Participants from both study groups will undergo ultrasound assessments after each menstrual cycle. These assessments will continue until either the cysts dissipate or for a maximum duration of three months.2.
**Menstrual pattern changes:** To observe shifts in menstrual patterns, we will have participants maintain menstrual diaries. Participants will record information regarding the frequency, regularity, duration, and volume of their menstrual cycles. Data will be collected at each follow-up appointment, allowing us to track any changes over time.

**Safety assessment:**
1.
**Duration of treatment:** We will determine the duration of treatment necessary for each participant by monitoring their response and progress during follow-up appointments. The treatment duration will be based on individual responses and the predefined treatment protocol.2.
**Monitoring side effects:** Participants will be encouraged to report any potential side effects during regular follow-up appointments and will also have access to a dedicated contact point for immediate reporting. Adverse events, including nausea, vomiting, weight gain, and acne, will be documented and assessed for severity and causality.3.
**Effects on liver function tests:** We will conduct regular blood tests to assess liver function. Liver function tests, including alanine aminotransferase (ALT) and aspartate aminotransferase (AST) levels, will be measured at specific intervals during the study. Any abnormal results will be monitored closely.4.
**Tracking critical complications:** We will monitor for critical complications such as thromboembolism, delayed menstrual cycles post-treatment, and potential interactions with other drugs through continuous review of participants’ medical records and regular assessments during follow-up appointments. In the event of a critical complication, immediate actions will be taken following our predefined clinical management plan.

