### Interventions

Participants in Group A will receive a course of ethinyl estradiol (0.03 mg) + Levonorgestrel (0.15 mg) combined oral contraceptive pills over three menstrual cycles. In Group B, participants will be administered dydrogesterone, with 10 mg taken twice daily for ten days during the luteal phase. This protocol will be repeated across three consecutive menstrual cycles.

Criteria for discontinuing or modifying allocated interventions will be clearly defined in our study. These criteria may include, but are not limited to, the development of severe adverse events, non-compliance with the treatment protocols, or the emergence of conditions that contraindicate further participation. In such cases, the participant will be withdrawn from the study, and the reasons for discontinuation or modification will be documented.

To ensure participant adherence to allocated interventions, we will implement the following strategies:
•Regular follow-up appointments and reminders to participants regarding treatment regimens.•Monitoring of participant compliance through self-reporting and pill counts for both intervention groups.•Tracking participant satisfaction and addressing any concerns or issues that may affect adherence.•Continuous communication between the research team and participants to address any questions or issues related to the interventions.

Participants will be advised to avoid the use of other hormonal medications or treatments during the study period, as these may confound the results. However, the use of non-hormonal over-the-counter medications will be allowed as needed, and these instances will be recorded.

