### Statistical analysis

The statistical analysis plan for this study will involve several key steps. Descriptive statistics will be used to summarize baseline characteristics of participants in both treatment groups. Continuous variables will be presented as means with standard deviations or medians with interquartile ranges, while categorical variables will be summarized as frequencies and percentages.

For the primary outcomes, the effectiveness and safety of the two treatments will be assessed separately. The regression of cysts within the three-month timeframe will be compared between groups using appropriate statistical tests, such as the Chi-square test or Fisher’s exact test. Changes in the menstrual pattern will be analyzed using paired t-tests or non-parametric tests if assumptions are not met.

Safety outcomes, including the duration of treatment needed and the incidence of side effects, will be compared using appropriate statistical tests, depending on the distribution of data. The impact on liver function tests and the occurrence of serious complications will be analyzed using appropriate statistical methods, potentially logistic regression, or survival analysis for time-to-event outcomes.

A comparative analysis between the two treatment groups will be performed using appropriate statistical tests, such as t-tests, Mann-Whitney U tests, or chi-square tests, depending on the nature of the data. Adjustments for potential confounders, such as age, BMI, and baseline cyst characteristics, will be considered using regression models. The significance level for hypothesis testing will be set at 0.05, and all tests will be two-tailed. Confidence intervals will be calculated where relevant.

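### Treatment duration, a primary outcome, is fixed at three cycles in one section and set by individual response in another, so as written it is either constant or an undefined, capped time to cyst disappearance

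*Protocol article*

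**What the plan says.** Interventions describes Group A as receiving "combined oral contraceptive pills over three menstrual cycles" and says of the Group B regimen: "This protocol will be repeated across three consecutive menstrual cycles". The Abstract gives the same length for both arms.

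Under Primary outcome measures, the Safety assessment lists duration of treatment first and says: "We will determine the duration of treatment necessary for each participant by monitoring their response and progress during follow-up appointments". It continues: "The treatment duration will be based on individual responses and the predefined treatment protocol". The Abstract and the Discussion also count treatment duration among the primary outcomes.

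Ultrasound follows each cycle. The Effectiveness assessment says: "These assessments will continue until either the cysts dissipate or for a maximum duration of three months". The article does not say whether treatment also stops when the cyst has gone, or what duration is recorded for a cyst still present at three months. The discontinuation criteria in Interventions are given as examples, and resolution is not among them.

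For the analysis, the Statistical analysis section says: "Safety outcomes, including the duration of treatment needed and the incidence of side effects, will be compared using appropriate statistical tests", the choice to follow from how the data are distributed. For group comparisons in general it offers tests "such as t-tests, Mann-Whitney U tests, or chi-square tests, depending on the nature of the data". Survival methods appear once, in the sentence on liver tests and serious complications: "potentially logistic regression, or survival analysis for time-to-event outcomes". Cyst regression within three months has its own comparison, by chi-square or Fisher's exact test.

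**The concern.** A course of fixed length and a course whose length depends on response cannot both hold. Two investigators could handle a woman whose cyst has gone after cycle 1 differently, and each could claim to follow the protocol. The meaning of a declared primary outcome turns on which rule is used.

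Under the fixed rule the outcome has no variation among adherent women. Under the response rule it measures how quickly the cyst disappears. That is effectiveness, although it is filed under safety, and follow-up ends at three cycles, so it is unknown beyond that point for women who have not resolved. Choosing the test by the shape of the distribution does not deal with this, because the difficulty is censoring and not non-normality. A drug with many failures could then appear to need the same treatment duration as a drug with few.

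Under the response rule there is a further effect: women who resolve early take the drug for less time, so side-effect incidence may be compared over unequal exposure.

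**Working it through.** **Step 1. The two readings.** Let T be the cycle after which the cyst is first seen to have gone, and D the recorded duration.

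- Fixed course: D = 3 for every adherent woman. The variance is zero and no test can be run.
- Response-driven course: D = min(T, 3), so D is 1, 2 or 3. A woman with T = 3 and a woman who never resolves both have D = 3, unless a rule separates them. The article gives none.

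**Step 2. A hand example (assumed rates; the article gives none).** Arm A resolves 30%, 20% and 30% in cycles 1 to 3, with 20% unresolved. Arm B resolves 30%, 20% and 0%, with 50% unresolved.

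- Mean D, arm A: 0.3×1 + 0.2×2 + (0.3 + 0.2)×3 = 2.2
- Mean D, arm B: 0.3×1 + 0.2×2 + (0 + 0.5)×3 = 2.2

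The whole distribution of D is the same in both arms, yet resolution is 80% v 50%. This is a constructed worst case, so a range follows.

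**Step 3. Power over a range of patterns.** The article has no figure for duration or resolution to reproduce. Inputs: 42 per group (Sample size, before dropout), two-sided 0.05 (Statistical analysis), assumed resolution of 80% v 50% and 90% v 60%. The 42 serves only as a group size here. It does not follow from the printed expression, 2×(1.96 + 0.09)²×1²/0.09² = 1038, but that is a separate point.

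- *Late pattern* (arms differ only at cycle 3). For 80% v 50%: A = 20/20/40% with 20% unresolved; B = 20/20/10% with 50% unresolved. For 90% v 60%: A = 20/20/50% with 10% unresolved; B = 20/20/20% with 40% unresolved. Mean D = 0.2×1 + 0.2×2 + 0.6×3 = 2.40 in every arm.
- *Even pattern* (constant chance h of resolving per cycle). With R resolved by cycle 3, h = 1 − (1 − R)^(1/3), and mean D = 1 + (1 − h) + (1 − h)². For R = 0.8, h = 0.415 and mean D = 1.93; for R = 0.5, h = 0.206 and mean D = 2.42. For 90% v 60%, mean D is 1.68 v 2.28.

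Power from 3,000 simulated trials per row:

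| Resolved, pattern | Mann-Whitney on D | t-test on D | Log-rank, censored at 3 | Chi-square on regression | Fisher on regression |
|---|---|---|---|---|---|
| 80% v 50%, late | 5% | 5% | 56% | 86% | 80% |
| 80% v 50%, even | 78% | 77% | 88% | 85% | 79% |
| 90% v 60%, late | 6% | 6% | 56% | 92% | 89% |
| 90% v 60%, even | 89% | 90% | 95% | 92% | 87% |

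At 46 per group the results are within about 4 points of these. Complementary log-log regression, a discrete-time method, behaves much like log-rank: about 57% in the Step 2 example and about 87% for 80% v 50% in the even pattern.

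**Step 4. Exposure, under the response-driven reading only.** In the even pattern the slower arm takes 2.42/1.93 = 1.25 times as many cycles (80% v 50%), or 2.28/1.68 = 1.36 times (90% v 60%). In the late pattern exposure is equal, 2.40 v 2.40. Under a fixed course there is no planned difference.

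**The case against.** A reader might infer that the plan commits to an uncensored test of duration. It does not. The Statistical analysis section names no test for this outcome, the next sentence of the same paragraph mentions survival analysis, and nothing in the article gives an unresolved cyst the value 3. Coding and censoring rules are commonly left to an analysis plan, which is not shown. What can be said is that the stated criterion for choosing a test permits such an analysis and does not point away from it.

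A reader might also infer that the trial could miss a large difference in cyst resolution. The documents do not support that either. Regression within three months is the first-listed primary outcome and has its own between-group test, with about 79–92% power in the four patterns above. In the late pattern that test does better than any time-to-event method, so a censored analysis of duration adds to it and cannot replace it.

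The near-total loss of power needs the arms to separate only at the last cycle. If the difference builds evenly, the uncensored tests lose only about 6 to 11 points against log-rank. Unequal exposure arises only under one of the two readings, and cumulative incidence by randomised arm remains a legitimate comparison. Which heading duration sits under changes no test by itself.

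None of this removes the conflict over treatment length or supplies a definition of the outcome.

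**Conclusion.** The point holds for the duration outcome and no further. The article states two rules for treatment length that do not agree. Under one, a declared primary outcome is constant among adherent women; under the other, it is a capped time to cyst disappearance with no stated value for women who do not resolve.

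The size depends on the reading and on the pattern of resolution. A fixed course leaves nothing to compare. With a response-driven course, assumed resolution of 80% v 50% and 42 per group, an uncensored test has between about 5% power (difference only at cycle 3) and about 77–78% (difference spread evenly), against about 56% and 88% for log-rank. These figures rest on assumed rates and on unresolved cysts being recorded as three cycles. The contradiction rests on the text alone. It should be settled before recruitment, which Study status says has not begun.

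**What to change.** 1. Reconcile Interventions with the Safety assessment, so that one rule for treatment length is stated, including what happens when the cyst disappears early. The choice of rule belongs to the clinical team.
2. Define the outcome as cycles to cyst disappearance on the ultrasounds already planned, and report it under effectiveness. This definition works under either rule.
3. Analyse it as discrete time-to-event data over cycles 1, 2 and 3, with unresolved women censored at three cycles, for example by complementary log-log regression. Keep the planned chi-square or Fisher's exact test of regression by three months alongside it.
4. If the reconciled rule lets exposure differ between women, report side effects per cycle of exposure as well as by arm.

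The cost is a change of wording in the protocol and analysis plan and a small amount of extra analysis. No further visits, scans or participants are needed.

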### Allocation

The allocation sequence will be generated by a biostatistician, who is not directly involved in the enrolment process. The enrolment of participants will be conducted by clinical research coordinators, while the assignment of participants to interventions will be performed by a research pharmacist based on the allocation sequence. Due to the nature of the interventions, participants cannot be blinded. However, outcome assessors and data analysts will be blinded to the treatment assignments. Unblinding may be considered in the event of a medical emergency or if knowledge of the treatment assignment is deemed necessary for the safety and well-being of the participant. Unblinding will only occur when the unblinded status is required for clinical management.

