**Primary outcome measures:** The primary outcomes, centered around effectiveness and safety, encompass the regression of cysts, alterations in menstrual patterns, treatment duration, side effects, and complications. These outcomes holistically capture the impact of the interventions on both the physical and overall well-being of participants. Monitoring cyst regression and menstrual pattern changes offers insights into the interventions’ therapeutic effects, while evaluating safety profiles contributes to a comprehensive understanding of potential risks.

**Implications and future directions:** The findings of this study have far-reaching implications for clinical practice. The data generated from the study will aid clinicians in making informed treatment decisions, balancing effectiveness and safety considerations. Furthermore, this research sets the stage for more targeted investigations into the mechanisms of action of COC and dydrogesterone, potentially uncovering novel insights into the pathophysiology of functional ovarian cysts.

**Limitations and considerations:** It’s important to acknowledge potential limitations, such as the limited follow-up duration and the exclusive focus on two treatment options. Future studies could explore the effects of alternative interventions and longer-term outcomes, providing a more comprehensive understanding of functional ovarian cyst management.

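### Side effects are primary outcomes, but the stated way of collecting them does not standardise elicitation in unblinded women, so the comparison may partly reflect differential reporting

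*Protocol article*

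**What the plan says.** The Discussion of the protocol article places side effects among the primary outcomes: "The primary outcomes, centered around effectiveness and safety, encompass the regression of cysts, alterations in menstrual patterns, treatment duration, side effects, and complications". The abstract does the same, and the section on primary outcome measures includes them under its safety assessment.

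Item 2 of that safety assessment gives the collection method. It says "Participants will be encouraged to report any potential side effects during regular follow-up appointments" and that they "will also have access to a dedicated contact point for immediate reporting". It then names the events: "Adverse events, including nausea, vomiting, weight gain, and acne, will be documented and assessed for severity and causality".

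On blinding, the second Allocation section says "Due to the nature of the interventions, participants cannot be blinded", and adds that "outcome assessors and data analysts will be blinded to the treatment assignments".

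The section on adverse events and unintended effects opens with a general commitment: "We will implement systematic procedures for collecting, assessing, reporting, and managing adverse events". It continues: "Adverse events will be documented by the clinical research team, assessed for causality and severity".

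The statistical analysis section then compares the incidence of side effects between the groups. All tests are two-tailed at 0.05.

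**The concern.** A recorded side effect needs two things: the woman has the symptom, and the symptom reaches the record. Randomisation balances the first, apart from any drug effect. Only uniform elicitation balances the second. Where women know their treatment and the stated method is to encourage them to report, the probability of recording can differ between arms for reasons other than the drug, such as what a woman expects from it or how readily she mentions a minor complaint.

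If that happens, a reporting difference appears in a primary outcome as a tolerability difference. It could create a difference, mask one or exaggerate one. Blinded grading and blinded analysis come too late to correct it, because a symptom that was never mentioned cannot be graded or analysed.

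**Working it through.** The plan gives no figure for side-effect incidence or reporting, so there is nothing to reproduce. The check has two parts.

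**1. The text, outcome by outcome**

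- Menstrual pattern: women keep diaries, and the data are collected at each follow-up appointment.
- Liver function: ALT and AST are measured at intervals.
- Critical complications: medical records are reviewed, with assessments at follow-up.
- Side effects: women are encouraged to report them, at visits or through the contact point. No set questions, symptom list to be asked, or measurement is named.

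Side effects are thus the one group for which the stated route is the woman's own report without a stated instrument. Two other statements bear on this. Assessor blinding acts after a report has been made. The commitment to systematic procedures covers collection in general terms, but does not say how a symptom is elicited.

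**2. Illustration of size**

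Let p be the true incidence, equal in both arms, and r1 and r2 the proportions of affected women whose symptom is recorded in each arm. Recorded incidence is p × r1 and p × r2, and the apparent ratio is r1/r2. All values of p, r1 and r2 are assumptions; the article gives none. Which arm has the higher r is also left open.

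With p = 20%:

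- r1 = 80%, r2 = 70%: 0.20 × 0.80 = 16% and 0.20 × 0.70 = 14%; ratio 0.16/0.14 = 1.14.
- r1 = 80%, r2 = 50%: 0.20 × 0.80 = 16% and 0.20 × 0.50 = 10%; ratio 0.16/0.10 = 1.6.

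With the 42 evaluable women per group stated in the sample size section, the second case means 42 × 0.16 = 6.7 against 42 × 0.10 = 4.2 women expected with a recorded event.

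The chance of a significant result when the true incidences are equal can be found by summing, over all pairs of binomial counts at 42 per group, the probability of those pairs for which the two-sided test rejects at 0.05:

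| True incidence, both arms | Reporting | Recorded | Chi-square, uncorrected | Fisher's exact |
|---|---|---|---|---|
| 20% | 80% vs 80% | 16% vs 16% | 5.3% | 2.8% |
| 20% | 80% vs 70% | 16% vs 14% | 6.2% | 3.2% |
| 20% | 80% vs 50% | 16% vs 10% | 13.6% | 7.6% |
| 40% | 80% vs 50% | 32% vs 20% | 24.3% | 17.9% |

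A small reporting difference barely moves the error rate. A large one raises it well above 5%, and more so for common symptoms. The article does not show which of these applies.

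**The case against.** The strongest objection is that a journal article condenses a fuller protocol. Checklist wording and visit forms commonly sit elsewhere, the article does promise systematic collection, and encouragement to report at a scheduled appointment is compatible with being asked. Part of this stands: a reader should not conclude that reporting is purely spontaneous, because the article never says so. What remains is that the article does state a method for these outcomes, and that method does not standardise elicitation.

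Three further readings are tempting but unsupported.

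- *Weight gain is left to self-report.* The article names no source for weight during follow-up, and BMI is needed for eligibility. Weight gain and acne can both be observed, so the point is strongest for nausea and vomiting.
- *Causality is judged by staff who know the arm, which biases a count of drug-related events.* The article does not say whether those judging causality are blinded. The planned comparison is of side-effect incidence, not of events judged drug-related.
- *The comparison does reflect expectation, with more reporting on the contraceptive pill.* Both arms receive active hormonal treatment, and nothing in the article gives a direction or size for differential reporting.

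It is also fair to object that a woman answering a checklist still knows her drug. A checklist evens out which symptoms are raised; it does not remove expectation from the answers.

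**Conclusion.** The point holds in a limited form. Side effects are primary outcomes compared between arms, the women are unblinded, and the stated collection method does not ensure that symptoms are elicited alike in both arms. The comparison may therefore partly reflect differential reporting, and neither assessor blinding nor the general promise of systematic collection rules this out.

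The size is unknown. Under the assumed 20% true incidence in both arms, the apparent ratio is 1.14 with 80% versus 70% reporting and 1.6 with 80% versus 50%; with equal reporting there is no distortion. The conclusion rests on the possibility of unequal reporting, not on evidence that it will occur. It is worth acting on because the article says that the study has not started and because an event never elicited cannot be recovered at analysis.

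**What to change.** Revise item 2 of the safety assessment so that:

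- a fixed symptom checklist is asked in identical words in both arms, at baseline and at each existing follow-up visit;
- weight gain is defined from weight measured at those visits;
- acne is graded by the outcome assessor, who is already to be blinded;
- the contact point stays for urgent reports;
- the between-arm comparison stays on all recorded events, as the statistical analysis section implies;
- the text acknowledges that open-label expectation can still affect the answers.

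The cost is a short form, a weighing and a few minutes at visits that already take place after each cycle. More low-grade events will be recorded in both arms. No visit is added and treatment is unchanged.

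If the full protocol already contains such a checklist, a sentence in this item saying so would settle the elicitation part of the point.
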